### 9.5 Analysis

9.5.1 Stage 1

Dose escalation is based on DLT and the decision rules as outlined above. As noted above, between-dose comparisons to select the fluconazole dose(s) to carry forward will largely be descriptive and not formally powered as all information will be factored into this decision.

9.5.2 Stage 2

In this pilot, we intend to combine the data over both Stages for the ampho B-based cohorts and for fluconazole doses that are tested in Stage 2. As noted above, only the confidence interval around the observed DLT rate in each dose will be adjusted for the dose escalation scheme. Analyses will employ appropriate methods such as Fisher’s exact test to compare dichotomous outcomes (e.g., Grades 3 and 4 events; CSF clearance before week 10) between doses or drugs, and t-tests or Wilcoxon tests to compare continuous covariates between two groups (or ANOVA or Kruskall-Wallis tests if three groups including ampho B). In the event all three fluconazole doses are evaluated in Stage 2, tests for trend such as ANCOVA, Cochran-Armitage and Jonckheere-Terpstra tests will be performed. Survival and other measures of time-to-event from study entry will be summarized with Kaplan-Meier estimates and, where appropriate, tested with log rank tests and possibly proportional hazards regression. The duration of the initial hospitalization will need to consider the duration of hospitalization preceding study entry. The focused neurological exam will be analyzed both on an item-by-item basis and also as a summary measure using methods such as mixed models analysis of variance or GEE that accommodate missing data and changing covariates.

The content and schedule of reports to be available to the core team, the SMC, and the full team will be detailed in the Study Monitoring Plan that will be developed prior to the opening of accrual to the study.

## 10.0 PHARMACOLOGY PLAN

**Pharmacology evaluations will be conducted only on samples collected from participants receiving study-provided fluconazole for the induction phase of treatment.** The pharmacology plan is described under the assumption that two of the three **Step 1** fluconazole **induction** doses tested in Stage 1 will be tested in Stage 2. Should all three doses be tested in Stage 2, appropriate modifications will be made to the hypotheses, and more modeling may be performed across the dose range. Should only one dose be tested in Stage 2, some analyses (eg, multicovariate modeling) will not be pursued. However, between-dose testing, albeit with lower power, could elucidate why only one dose had evidence of both tolerability and efficacy in Stage 1. Because of the possibility of drug-drug interactions with RIF and/or EFV, a number of objectives are restricted to being evaluated in samples from participants who did not receive these drugs. The objectives confined to those receiving RIF and/or EFV will only be pursued if sufficient numbers of participants receive these drugs and have the appropriate samples collected from them.

### 10.1 Pharmacology Objectives

10.1.1 Primary Objective

Compare concentrations of fluconazole in plasma and CSF at steady state for the doses tested in Stage 2. Samples from participants taking RIF or EFV at the week 2 PK collection will not be used in this comparison.

10.1.2 Secondary Objectives (for samples from participants who were not taking RIF or EFV at the week 2 PK collection)

10.1.2.1 Evaluate the relationship of fluconazole dose to fluconazole trough concentrations in plasma and CSF at steady state across the range of all induction doses studied.

10.1.2.2 Evaluate the relationship between fluconazole plasma and CSF concentrations in the doses tested in Stage 2 and change in cryptococcal concentration in CSF from baseline to week 2 and time to CSF sterility.

10.1.2.3 Evaluate the relationship between fluconazole plasma and CSF concentrations in the doses tested in Stage 2 and fluconazole toxicity or intolerance independent of dose as defined by Grade ≥ 3 toxicity, change in dose, or discontinuation of fluconazole.

10.1.2.4 Evaluate the relationship between fluconazole dose and plasma concentrations before and after dose reductions for toxicity or intolerance in the doses tested in Stage 2 (within-participant dose-to-plasma concentration comparisons).

10.1.2.5 Evaluate the relationship of fluconazole plasma and CSF concentrations with dose and demographic and physiological characteristics of participants including, but not limited to sex, weight, body mass index, and creatinine clearance.

10.1.2.6 Evaluate relationship of self-reported adherence to plasma and CSF trough fluconazole concentrations and to efficacy.

10.1.3 Secondary Objectives (for samples from participants who were taking RIF or EFV at the week 2 PK collection)

10.1.3.1 Evaluate plasma and CSF concentrations of fluconazole alone versus fluconazole when given concomitantly with RIF in the 1600 mg and 2000 mg daily doses, if sufficient numbers of samples are available.

10.1.3.2 Evaluate plasma and CSF concentrations of fluconazole alone at the 1600 mg and 2000 mg daily doses versus fluconazole given concomitantly with EFV, if sufficient numbers of samples are available.

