2.1.1 Fluconazole

Fluconazole is a synthetic triazole antifungal agent. It is a highly selective inhibitor of fungal cytochrome P450-dependent sterol C-14 alpha-demethylation. The subsequent loss of normal sterols correlates with the accumulation of 14 alpha-methyl sterols in fungi and may be responsible for the fungistatic activity of fluconazole.

The pharmacology of fluconazole has been well studied only at doses of 50-400 mg per day. It is well absorbed orally (~ 90%), with peak plasma concentrations reached within 1-3 hours after dosing, and is not affected by food. Peak plasma concentrations at steady state on daily dosing are usually about twice those at trough. Fluconazole is minimally protein bound, widely distributed in body water with an apparent volume of 0.7 L/kg, and 80% is excreted unchanged in the urine with a half-life of 25-30 hours. About 11% is excreted in the urine as the glucuronide and N-oxide metabolites, which are both inactive and probably come from metabolism in the liver by cytochrome P450 3A4 enzymes. Renal insufficiency markedly prolongs the excretion of the drug.

Steady state is reached in plasma in 5-10 days on daily dosing, with steady state plasma concentrations of 4.6 and 9 mg/L after 200 and 400 mg doses, respectively. Cerebrospinal fluid (CSF) levels are 50-90% of those in serum [Foulds, 1988]. Over the range of 100–400 mg orally, the variation of fluconazole maximum plasma concentration (Cmax) and area under the concentration–time curve (AUC) are proportional to the administered dose. The elimination half-life and the time of Cmax also remain constant in this dosing range. This indicates the linearity of the pharmacokinetics (PK) of fluconazole for oral doses of 50-400 mg [Tett, 1995; data on file with Pfizer].

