5.1.2 Fluconazole Dosage Adjustments

Dose modification of fluconazole is only permitted for renal impairment, intolerability, toxicity, or during the induction step for weight. Weight-based modifications must be implemented at the first dose. Specific guidelines are provided in section 7.4.

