6.3.7 Study Treatment Modifications

All modifications to ampho B-based regimens or to study-provided fluconazole, including initial doses, participant-initiated and/or protocol-mandated interruptions of 2 or more consecutive days, any modifications, and any permanent discontinuation of treatment will be recorded on the CRFs at each visit and keyed within 48 hours. Participant-initiated and protocol-mandated interruptions include both inadvertent and deliberate interruptions of the ampho B-based regimens or of study-provided fluconazole.

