## 7.0 CLINICAL MANAGEMENT ISSUES

A5225/HiFLAC sites must follow the DAIDS Table for Grading the Severity of Adult and Pediatric Adverse Events Version 1.0, December 2004, which can be found on the DAIDS DAIDS RSC Web site: <http://rsc.tech-res.com/safetyandpharmacovigilance/>, for grading toxicities related to study treatment.

Toxicity management at non-US CRSs may require reliance on clinical symptoms, clinician judgment, and available laboratory markers, since alternatives to study-provided treatment may be very limited and baseline levels may be different from those in other settings. It is understood that treating physicians will provide whatever available treatment is considered best to protect patient safety and well-being; compliance with study requirements must not compromise such treatment.

This section provides guidelines for management of toxicities related to **study-provided** fluconazole. Management of toxicities thought to be related to ampho B will be according to local standard of care. Guidelines for use of ampho B and management of the most common toxicities associated with it are included in section 5 of the A5225/HiFLAC MOPS and may be consulted, at the discretion of the site investigator.

Participants who permanently discontinue either fluconazole or **any** ampho B**-based regimen** because of an AE should be followed closely until resolution of the AE can be documented.

In the subsections below, ‘interruption’ is used to mean a temporary discontinuation, while ‘discontinuation’ is used to mean a permanent discontinuation. If study-provided fluconazole is interrupted for longer than 3 consecutive days, it must be discontinued and the participant must immediately be treated according to local standard of care (SoC).

The A5225/HiFLAC core team must be notified via e-mail ([[contact]](mailto:[contact])) within 3 business days after premature discontinuation of fluconazole or ampho B in Step 1 or Step 2.

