### 7.4 Fluconazole Dose Modifications

- - 1. Renal Impairment

The initial fluconazole dose will be given as specified, independent of the screening creatinine clearance. Subsequently, doses **of study-provided fluconazole** should be adjusted according to the table below for subjects with decreased creatinine clearance. **Dose adjustments to fluconazole that is given in combination with ampho B are also important; refer to the package insert for guidance.**

Table 7-1

| Creatinine Clearance  (Measured or Estimated) | Fluconazole Dose |
| --- | --- |
| ≥ 50 mL/min | current dose |
| 20 - 49 mL/min | 50% current dose |
| 0 – 19 mL/min | 25% current dose |

- - 1. Body Weight < 60 kg at Study Entry

The following adjustments should be made in the induction dose of fluconazole for participants whose weight at entry is < 60 kg. All adjusted doses of fluconazole should be rounded up to the nearest 200 mg, based on the participant’s actual weight. For example, if a participant in Cohort 1 weighs 42 kg, 42 kg X 20 mg/kg = 840 mg; dose should be rounded up to 1000 mg. Weight-based adjustments must NOT be made to any consolidation or maintenance doses of fluconazole.

Table 7-2

| Weight at Entry | Weight-Adjusted Daily Fluconazole Dose for Induction Step | | |
| --- | --- | --- | --- |
| For 1200 mg cohorts | For 1600 mg cohorts | For 2000 mg cohorts |
| < 60 kg | 20 mg/kg up to 1200 mg total | 26 mg/kg up to 1600 mg total | 33 mg/kg up to 2000 mg total |

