## 8.0 CRITERIA FOR PREMATURE TREATMENT OR STUDY DISCONTINUATION

### 8.1 Treatment Discontinuation

- **Failure to have CM confirmed by Day 5 by testing performed at a DAIDS-approved laboratory**
- Fluconazole-related dose-limiting or ampho B-related treatment-limiting toxicity (see section 7.0, Clinical Management Issues or section 5.0, A5225/HiFLAC MOPS).
- Pregnancy or breast-feeding (for fluconazole).
- Interruption of oral fluconazole for any reason for more than 3 consecutive days.
- Requirement for prohibited concomitant medications (see current A5225/HiFLAC MOPS).
- Clinical reasons believed life threatening by the physician, even if not addressed in the clinical management section of the protocol.

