### 10.3 Primary and Secondary Data Analysis

The primary analysis will be a two-group t-test comparing the natural-log transformed plasma and CSF concentrations between all evaluable participants taking the doses tested in Stage 2 (i.e., participants taking these doses in Stages 1 and 2).

Secondary analyses will use various generalized linear models (e.g., standard regression for assessing impact of body mass index (BMI), race, gender, etc. on the trough concentrations; logistic regression for assessing impact of trough concentrations on toxicity, etc).

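### Pharmacology objective 10.1.2.3 counts any fluconazole dose change or stop as toxicity whatever its cause, so renal dose adjustments can create a spurious link between drug level and toxicity (minor).

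*Protocol*

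**What the plan says.** Objective 10.1.2.3 of the protocol asks how plasma and CSF concentrations relate to "fluconazole toxicity or intolerance independent of dose as defined by Grade ≥ 3 toxicity, change in dose, or discontinuation of fluconazole". The three parts are alternatives. Neither the dose-change part nor the discontinuation part carries a cause. Section 10.3 names the model: "logistic regression for assessing impact of trough concentrations on toxicity".

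Other sections allow or require dose changes and stops that are not toxicity:

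- Section 5.1.2: "Dose modification of fluconazole is only permitted for renal impairment, intolerability, toxicity, or during the induction step for weight".
- Section 7.4, renal impairment: after the first dose, doses "should be adjusted according to the table below for subjects with decreased creatinine clearance". Table 7-1 gives 50% of the current dose at 20–49 mL/min and 25% below that.
- Section 8.1 lists, as a reason to stop treatment, "Interruption of oral fluconazole for any reason for more than 3 consecutive days". Section 7.0 agrees: "If study-provided fluconazole is interrupted for longer than 3 consecutive days, it must be discontinued". Section 6.3.7 adds: "Participant-initiated and protocol-mandated interruptions include both inadvertent and deliberate interruptions".
- Section 8.1 also stops treatment for pregnancy, unconfirmed CM and prohibited medications.

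Section 2.1.1 says of fluconazole: "Renal insufficiency markedly prolongs the excretion of the drug". It puts the share excreted unchanged in urine at 80%.

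The protocol does state a cause elsewhere. Objective 10.1.2.4 is confined to dose reductions made for toxicity or intolerance, and the glossary's DLT definition requires a fluconazole-related toxicity.

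**The concern.** An outcome that mixes toxicity with unrelated events usually only loses power. Renal adjustment does more than that, because it is tied to the exposure being tested. The decline in clearance that triggers a Table 7-1 cut also raises the level at a given dose, and the cut then lowers it. A participant with a renal adjustment and no toxicity at all is therefore counted as an event and also sits away from the centre of the concentration distribution. Adjusting for assigned dose does not remove this, because the link acts within a dose level.

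At stake is the interpretation of the exposure–toxicity result. Level could appear to cause toxicity, or to protect against it, according to how many renal adjustments occur and when they are sampled.

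**Working it through.** The protocol gives no figure for this analysis, so there is none to reproduce. The check has two parts.

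**Text.** The cause is stated in 10.1.2.4 and in the DLT definition, and is absent from 10.1.2.3. Read literally, a Table 7-1 cut is a change in dose, and a stop after more than 3 days of inadvertent interruption is a discontinuation. Both meet the definition.

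**Inputs from the protocol.** 70 observations for secondary models and a within-dose CV of 25% (10.4); 80% excreted unchanged (2.1.1). The one observed spread, in the small 800–1000 mg monotherapy study in 2.1.1, is 41 ± 26 mcg/mL in serum: 26/41 = 0.63, taken as a CV of about 60%.

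**Assumptions, not in the protocol.** True toxicity in 20%, unrelated to level; renal dose changes in 5, 10 or 15%; creatinine clearance halved in those cases.

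**Level shift.**
- Relative clearance = 0.2 + 0.8 × 0.5 = 0.6, so the level before adjustment is 1/0.6 = 1.67 times usual.
- After the 50% cut it is 1.67 × 0.5 = 0.83 times usual.
- For a smaller decline (clearance down by a quarter): 0.2 + 0.8 × 0.75 = 0.8, so 1/0.8 = 1.25 times before the cut.

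**Simulation.** Logistic regression of the composite on log concentration with dose in the model, n = 70, two-sided 5% test, 1,000 to 2,000 replicates. The Monte Carlo standard error is at most √(0.5 × 0.5/1000) = 1.6 points. False-positive rates for renal changes in 5 / 10 / 15% of participants:

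| When the level is drawn | CV 25% | CV 60% |
|---|---|---|
| No non-toxicity events in the outcome | about 4–5% | about 4–5% |
| All before the cut, level × 1.67 | 28 / 64 / 86% | 10 / 21 / 34% |
| All before the cut, level × 1.25 | 10 / 21 / 34% | 6 / 8 / 9% |
| Half before, half after | 8 / 15 / 20% | about 5–9% |
| All after the cut, level × 0.83 | 8 / 16 / 24% | about 5–9% |

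The false association is upward for sampling before the cut and downward for sampling after it. Under mixed timing the two partly cancel: ln 1.67 = 0.51 against ln 0.83 = −0.18.

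A separate run without dose in the model gave the same pattern. At level × 1.5 the odds ratio per SD was 1.34 / 1.67 / 1.88, and at level × 0.75 it was 0.78 / 0.68 / 0.62.

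Stops unrelated to level (× 1, in 5 to 15% of participants) gave rejection of about 3–6%. They dilute the outcome but do not bias the test.

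**The case against.** **The wording implies a cause.** The term being defined is toxicity or intolerance, the neighbouring objective and the before-and-after sampling in 10.2 both concern reductions for toxicity, and section 9.2.3 leaves pharmacology to separate analysis plans. This lowers the severity. It does not remove the point, because 10.1.2.3 writes the definition out and a plan that follows it inherits the gap.

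**The large percentages are an extreme case.** This stands. The 28–86% figures need every renal case sampled before adjustment, a halved clearance and a CV of 25%. Chemistries are due on days 4 and 7 and at week 2, so some cuts would precede the week 2 sample. Entry requires clearance of at least 50 mL/min, so some participants would cross the threshold after only a small decline.

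**Missed doses.** A reader might infer a strong false protective effect, since missed doses lower the level and can force a stop. Simulated with the level at × 0.45 in 5 / 10% of participants, rejection is 47 / 85% at CV 25% and 18 / 42% at CV 60%. The protocol does not support this as the expected case. Section 6.3.24 reschedules PK collection when a dose was missed in the previous 3 days or on the day. What remains is the single sample taken when rescheduling fails, and the discontinuation sample if it is used.

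**Other named events scarcely enter.** Weight-based changes are made at the first dose. Stops for unconfirmed CM or HIV mostly come before week 2, and those participants leave the study. No link between pregnancy or prohibited drugs and the drug level is shown.

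**Dose selection.** A reader might also infer that the dose decisions are compromised. They are not: escalation and the MTD rest on DLT, which already requires relatedness, and the Stage 2 criteria in 9.3.2 do not use this model.

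**Conclusion.** The definition in 10.1.2.3 is too broad as written, and its renal component can bias the regression in 10.3 in either direction. The size cannot be fixed from the protocol. With n = 70 and assumed renal rates of 5 to 15%, the false-positive rate runs from about 5–9% (mixed or post-adjustment timing, CV 60%), through about 8–25% (same timing, CV 25%), to 28–86% (all sampled before adjustment at × 1.67, CV 25%). The last range is an upper bound and not the expected effect.

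The missed-dose route is mostly limited by 6.3.24, and other unrelated stops mainly dilute the outcome.

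Nor does the evidence support restricting the Grade ≥ 3 component to events the investigator judges related. That is debatable in an open-label trial, and nothing here shows the component to be at fault.

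Severity is minor: this is a secondary pharmacology objective, and no dose decision is shown to rest on it.

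**What to change.** In 10.1.2.3, limit the dose-change and discontinuation components to those whose recorded cause is fluconazole toxicity or intolerance, in line with 10.1.2.4. Add that Table 7-1 renal adjustments, scheduled step changes and stops for reasons other than toxicity are not outcome events. Leave the Grade ≥ 3 component as it is. No clinical rule changes.

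The cost is one or two sentences. Treatment modifications are already recorded (6.3.7), as are toxicities that lead to a treatment change (6.3.9, 6.3.13). The downsides are fewer outcome events and reliance on the recorded cause.

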Based on these data, coadministration of these two drugs is discouraged in A5225/HiFLAC. Furthermore, coadministration of NVP and fluconazole at fluconazole doses > 400 mg daily is prohibited in A5225/HiFLAC. While the decision regarding coadministration of NVP and fluconazole at fluconazole doses of ≤ 400 mg fluconazole daily is left to the discretion of the treating clinician, we strongly urge the institution of weekly monitoring of hepatic enzymes [Manosuthi 2007].

Limited data on the coadministration of fluconazole and EFV have demonstrated a small increase in EFV exposures with no change in fluconazole concentrations. Beginning at week 4, EFV may be used concomitantly with fluconazole without regard to fluconazole dose.

When zidovudine (ZDV) is administered at 200 mg every 8 hours concomitantly with 400 mg fluconazole daily, Cmax and AUC of ZDV were increased 84.2%, and 74.4%, respectively [Sahai 1994]. Therefore, caution should be used when coadministering these two drugs.

Limited data on the drug interaction between RIF and fluconazole demonstrate enhanced metabolism of concurrently administered fluconazole, thereby reducing the AUC of fluconazole by 23% [Apseloff 1991]. Therefore, the use of RIF is prohibited for A5225/HiFLAC study participants receiving 1200 mg daily fluconazole. RIF may be initiated after these participants have initiated the consolidation dose of 600 mg fluconazole daily (rather than 400 mg daily) or the maintenance dose of 200 mg daily fluconazole. Coadministration of fluconazole with RIF is permitted in the higher induction dose cohorts (1600 mg and 2000 mg daily), however, because the impact of any drug-drug interaction (i.e., the extent to which RIF will reduce fluconazole concentrations) is expected to be lessened at these doses. Medications that are prohibited from coadministration with fluconazole are listed in the A5225/HiFLAC Manual of Operations (MOPS) as are those that may be administered with caution.

Additional information can be obtained from the latest fluconazole package insert.

Considerations Regarding Participant Follow Up

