Dose adjustment guidelines for ampho B side effects are described in section 5 of the A5225/HiFLAC MOPS. Step 2 has been included in the protocol for participants who discontinue ampho B because of ampho B intolerance. Each site will be allowed to determine the appropriate Step 2 dose of fluconazole, either 800 mg daily or the maximum locally approved dose.

ART Initiation and Potential Drug-Drug Interactions

Evidence-based guidelines are not available for optimal timing of ART initiation in the setting of acute CM. Site clinicians may initiate ART when they feel it is appropriate to do so. However, because fluconazole substantially increases NVP levels and may increase hepatotoxicity [Geel 2004], NVP-based ART may be used only when participants are taking fluconazole at a dose of ≤ 400 mg. Because NVP-based ART is commonly employed in resource-limited settings, site clinicians are advised to seek alternative antiretroviral drugs (ARVs) for participants on higher doses of fluconazole.

There is the potential for two-way interactions between fluconazole and non-nucleoside reverse transcriptase inhibitors (NNRTIs) and drugs belonging to the class of protease inhibitors (PIs). As mentioned previously, fluconazole is an inhibitor of CYP450 3A4 and, to a lesser extent, 2C8, 2C9, and 2C19 [Niwa 2005]. Therefore, levels of medications that are substrates of CYP450 enzymes may be raised in the presence of fluconazole. These include the NNRTIs NVP and EFV, and the PIs nelfinavir, amprenavir, fosamprenavir, lopinavir, and atazanavir.

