6.3.6 ART (Initiation and Modification)

All modifications to ART must be recorded on the CRF. Modifications include initiation as well as any changes in dose or formulation, interruptions of 2 or more consecutive days, or discontinuations for any reason.

Although initiation of ART prior to week 4 is discouraged for participants taking high dose fluconazole, participants who initiate ART that does not contain NVP prior to Step 3 may remain on study. Participants who initiate NVP while taking high dose fluconazole (ie, at a dose higher than 400 mg daily) must be discontinued from study treatment.

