### 10.2 Pharmacology Study Design

10.2.1 Single sample for fluconazole at week 2

Plasma: At week 2, all participants in fluconazole induction cohorts will have whole blood collected for drug concentrations of fluconazole. For participants taking fluconazole once daily, the collection should take place 15-33 hours after the last dose of fluconazole and prior to the next dose of fluconazole. For participants taking fluconazole twice daily, the collection should take place 8-16 hrs after the last dose of fluconazole and prior to the next dose of fluconazole. For participants taking fluconazole more frequently than twice a day, sites should attempt to make the collection at least 4 hours after the most recent dose. The plasma PK sample should be obtained within 1 hour (ie, before or after) of the CSF collection described below.

CSF: A CSF sample must be obtained from all participants described in the paragraph above.

The date and time of the administration of all fluconazole doses for the previous 3 days and the day of the study visit as well as the date and time of plasma and CSF sampling will be recorded on the CRF.

- - 1. Single sample for fluconazole in participants taking RIF or EFV

Plasma: Whole blood will be collected for fluconazole concentrations and concentrations of the concomitant drug from all participants in the 1600 mg and 2000 mg daily fluconazole cohorts who are taking RIF and/or EFV (with no concomitant NVP) during the induction step. This collection should take place at least 2 weeks after the initiation of co-administration of fluconazole with the concomitant drug. For participants taking fluconazole once daily, the collection should take place 15-33 hours after the last dose of fluconazole and prior to the next dose of fluconazole. For participants taking fluconazole twice daily, the collection should take place 8-16 hrs after the last dose of fluconazole and prior to the next dose of fluconazole. For participants taking fluconazole more frequently than twice a day, sites should attempt to make the collection at least 4 hours after the most recent dose. The plasma sample should be obtained within 1 hour (i.e., before or after) of the CSF when CSF is collected as described below.

CSF: In addition, a CSF sample will be obtained for drug concentrations (if an LP is performed for other clinical or study purposes) from all participants taking part in this PK collection.

The following will be recorded on the CRF:

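### Sections 10.1.2 and 10.1.3 class PK samples by RIF/EFV use at week 2, so interaction samples from participants who start either drug later fall outside the objective they are drawn for

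*Protocol*

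**What the plan says.** Section 10.1 divides the secondary PK objectives by drug use at one visit. The heading of 10.1.2 is "Secondary Objectives (for samples from participants who were not taking RIF or EFV at the week 2 PK collection", and the heading of 10.1.3 is "Secondary Objectives (for samples from participants who were taking RIF or EFV at the week 2 PK collection". The week 2 visit may take place from day 12 to day 17 (6.2.2).

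Section 10.2 has a separate collection for RIF and EFV. It covers all participants in the 1600 and 2000 mg cohorts who take either drug during induction, and it fixes the timing: "This collection should take place at least 2 weeks after the initiation of co-administration of fluconazole with the concomitant drug".

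On when these drugs start:

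- Section 2.1.1 says of EFV: "Beginning at week 4, EFV may be used concomitantly with fluconazole without regard to fluconazole dose".
- Section 6.3.6 says that "initiation of ART prior to week 4 is discouraged for participants taking high dose fluconazole".
- Section 2.2 says: "Site clinicians may initiate ART when they feel it is appropriate to do so".
- The paragraph on IRIS in section 9.3 recommends holding ART until Step 3 or 4.
- RIF is permitted at 1600 and 2000 mg with no week 4 limit (2.1.1).

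On intent, section 2.2 (Pharmacology Studies) expects the EFV information to come from participants who begin EFV during induction. The opening of section 10.0 confines the fluconazole-alone objectives to participants who did not receive RIF or EFV. It allows the interaction objectives for those who did, if enough of them have suitable samples.

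**The concern.** The rule that selects the analysis set and the rule that schedules the sample point to different people. The headings look at the participant's status at week 2. The collection looks at status at any time in induction and then waits 2 weeks. A participant who starts RIF or EFV between those two points gives the dedicated sample but does not belong to the set that would use it.

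The same participant meets the heading of 10.1.2. Nothing in that heading removes later samples taken on RIF or EFV. The clearest case is the post-reduction sample for 10.1.2.4, which 10.2 takes at least 2 weeks after a dose reduction. Section 7.1 gives a separate reduced level for participants on RIF, so a co-treated post-reduction sample is foreseen.

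At stake is information that the protocol says is missing elsewhere. Section 2.2 reports no EFV interaction data above 400 mg/day, and section 10.5 says that neither combination has been studied at these doses. The interaction objectives go ahead only if numbers suffice, so a set that leaves out valid samples makes it more likely that they are dropped.

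**Working it through.** **The plan's own PK figure.** Section 10.4 takes 40 participants per dose, allows 5 for RIF/EFV use at week 2 or too little CSF, and so works with 35. It assumes a CV of 25%, a difference of about 20% of the lower mean, 90% power and two-sided alpha 0.05.

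- Raw scale: n = 2(1.960 + 1.282)² × 0.25² / 0.20² = 32.8, so 33 per group. Power at 35 is 91.7%.
- Log scale, as 10.3 analyses it: SD = √ln(1 + 0.25²) = 0.246 and ln 1.2 = 0.182, so n = 39. Power at 35 is 87.2%, and the difference detectable with 90% power is 21%.

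The stated figure reproduces to within its own approximation. It concerns the primary dose comparison and does not depend on this point.

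**Day arithmetic.** The inputs are the week 2 draw on day 12 to 17 (6.2.2), an interaction sample no earlier than start + 14 days (10.2), EFV from week 4, taken as day 28 (2.1.1), and induction lasting 4 to 10 weeks (Schema).

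| Co-administration starts | On drug at the week 2 draw? | Earliest interaction sample | Class under the headings |
|---|---|---|---|
| Day 0 to 3 (including drug already taken at entry) | Yes | Day 14 to 17 | 10.1.3; the week 2 draw can itself serve if late enough in its window |
| Day 4 up to the draw (day 17 at the latest) | Yes | Day 18 to 31 | 10.1.3, through a later sample |
| After the draw, for example day 28 | No | Day 42 | Outside 10.1.3, inside 10.1.2 |

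For EFV started at week 4, 28 + 14 = 42, which is 42 − 17 = 25 days after the last possible week 2 draw. Induction ends by week 10 (day 70), so the latest start that still leaves room for an induction sample is 70 − 14 = day 56. Every EFV start from day 28 to day 56 that yields an interaction sample in induction therefore falls outside 10.1.3. The same holds for RIF started after the draw.

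**Headings against section 10.0.** A participant who starts RIF or EFV after the draw was not taking it at week 2, so meets the 10.1.2 heading. The same participant did receive the drug, so does not meet the restriction in 10.0. The two statements give different answers for the same person.

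**The case against.** The strongest reply is that the intent is clear and the slip is one of wording. Section 10.0 does not tie either group to week 2, section 2.2 names EFV started in induction, and 10.1.3.2 speaks of EFV given concomitantly. The 10.1.3 heading can hardly be meant literally, since its own objectives compare with fluconazole alone and the heading supplies no such comparator. These are exploratory objectives (1.4.2), and section 9.2.3 leaves their analysis to separate plans that are not shown. All of that stands and limits the weight of the point. It does not remove it: the headings state a rule, and that rule conflicts with 10.0 and 10.2.

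The number of samples affected may also be small. Participants who clear early can leave induction from about week 4, and ART is advised for Step 3 or 4, so few may be on EFV and still in induction at day 42. The protocol gives no count.

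A reader might go further in three ways that the documents do not support.

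- That all interaction samples are excluded. Week 4 is a permission joined to advice against earlier ART, not a bar. RIF has no such limit at 1600 and 2000 mg, and 10.4 allows for some RIF or EFV users at week 2.
- That participants who start between about day 4 and the draw are analysed before the 2-week wait is met. The wait in 10.2 still governs their interaction sample, and they stay in 10.1.3 through it.
- That the fluconazole-alone set is biased by a known amount. The 23% fall in fluconazole AUC with RIF (2.1.1) cannot be set against the 20% in 10.4, which is a difference between two dose means at week 2. For EFV, 2.1.1 reports no change in fluconazole levels, on limited data.

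**Conclusion.** The point holds as a conflict between the headings of 10.1.2 and 10.1.3 and the protocol's own sampling plan and stated intent. Samples from participants who start RIF or EFV after the week 2 draw are outside the objective they were collected for, and later co-treated samples from the same participants are inside the set meant to be free of these drugs.

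Its reach is limited. Participants on either drug by the week 2 draw are included. The primary PK comparison uses the week 2 collection and already removes users at that visit, so it is unaffected. No efficacy or dose-limiting toxicity analysis depends on it. How many samples are lost or misplaced cannot be worked out from the protocol. The conclusion rests on reading the headings as they stand and on taking week 4 as day 28.

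**What to change.** Reword the headings of 10.1.2 and 10.1.3 so that each sample is classed by RIF/EFV use when it is taken:

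- Interaction samples: those collected under 10.2 during induction, after at least 2 weeks of co-administration.
- Fluconazole-alone samples: those taken while the participant is on neither RIF nor EFV.

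Make the opening of section 10.0 and the analysis text in 10.3 agree. Where a participant also has a week 2 sample without the drug, a within-participant comparison of the later level with the week 2 level may be added as a supportive analysis. Which comparison should lead is a matter of choice and need not change.

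The cost is wording only. ART changes, TB therapy, fluconazole, RIF and EFV dose times and the samples themselves are already recorded or collected (6.3.5, 6.3.6, 10.2). One small downside is that the paired comparison is limited to participants still in induction when the later sample is taken.
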